### Mechanisms of action and process evaluation

Changes in overall mindful awareness, self-compassion, and catastrophic beliefs are hypothesised to be potential underlying working mechanisms of MBCP leading to positive changes in mental health and behaviour during the perinatal period. Overall mindful awareness including qualities such as observing, describing, acting with awareness, non-judging and non-reactivity to inner experience, will be assessed by the Five Facet Mindfulness Questionnaire (FFMQ) [81]. In addition, mindful awareness specifically related to one’s role as a (new) parent will be assessed with the Interpersonal Mindfulness in Parenting Scale (IM-P) [82]. Self-compassion will be assessed by the Self-Compassion Scale-Short Form (SCS- SF) [83], and catastrophic beliefs will be assessed by the Perinatal Disaster Scenarios Scale (PDSS).

Expectancy effects in women and partners will be assessed by the question: “If you had a choice, which one of the study’s programmes would you prefer to participate in?”. Adherence to MBCP will be assessed by number of classes attended and weekly diaries of the number of minutes spent in formal meditation practice each week between sessions. Data regarding the number of attended sessions of FoCC will also be collected.

### Cost-effectiveness evaluation

The evaluation of cost-effectiveness will be carried out from a societal and health care perspective including direct and indirect costs, with an average time frame of six months following study inclusion. Participants will fill out a standardized Perinatal Health Care-costs Questionnaire (PHCQ) in which they are retrospectively asked how often they had contact with the health care system, including type, duration, medications used, number of days absent from work, production losses, and professional and family support. At T1participants are asked to report any contacts with the healthcare system from the time of first knowledge of pregnancy to the start of MBCP or FoCC - which contains information about the past three to five months; from T1 till T4 participants report about the past three months. Costs of both programmes will be calculated separately based on the duration and frequency of sessions and group size. Costs will be derived by multiplying the resources used by the unit price of each resource. Unit prices will be based on Dutch standard prices from the Dutch Guideline of Cost Research [84] or other published unit prices. The costs of the interventions will be based on the standardized hourly pay of midwives and the invested intervention related educational costs. The EQ-5D [73] is administrated to provide utilities and to calculate quality adjusted life years (QALY’s).

### Recruitment

Figure 2 provides an overview of the recruitment and study procedures. Recruitment for this study started in April 2014. Midwives and obstetricians were briefed on the study at workshops and fraternity meetings. Pregnant women are invited to join the study in two ways: via advertisement posters and brochures in midwifery waiting rooms inviting them to visit the study’s website http://www.mbcpmidwife.nl/ or by midwives and obstetricians who find they are caring for a highly anxious and/or stressed pregnant woman and offer them information about the study. After a potentially eligible pregnant woman or her care provider contacts the research team, informed consent is obtained. Subsequently, the pregnant woman completes an online screening questionnaire (W-DEQ-A) [3]. Questionnaire responses are scored within 48 h. Women who score ≥66 on the W-DEQ-A are contacted by telephone and the study’s two-stage exclusion protocol is administered. After this procedure, the eligible participant’s partner is invited to join the study, informed consent is obtained and the two-step exclusion interview is administered.

The first step of the exclusion protocol is carried out by the research midwife by telephone in order to identify a current risk for a psychosis/psychotic disorder, potential suicidal risk, substance abuse and dependency, or borderline personality disorder in the woman and/or her partner. In cases where any of the above risks or disorders are suspected, an extensive personal psychological interview is conducted by a trained psychologist using the Structured Clinical Interview for DSM-IV disorders Axis I and Axis II (SCID-I and SCID-II) [64]. Subsequently the general physician of the participant is informed of the existing or risk for a particular mental disorder.

Recruitment will continue until at least 64 participants with a W-DEQ-A score ≥66 have completed the study’s programme in each of two study arms.

### Quasi-experimental allocation to the two study conditions

The allocation to the two study groups will be done on the sequence of entry into the study using an Excel program of created codes. This procedure ensures that the referral midwives and obstetricians are not able to predict the group to which the participant will be assigned. The choice for quasi-experimental allocation is based on a steadily increasing gestational age, dependence on recruitment speed and efficiency, and the required minimum group size of six participants in the MBCP intervention group.

### Statistical analyses

#### Primary analyses

Dichotomous outcome data will be analysed using Chi-square tests or logistic regression using the method of ‘last observation carried forward’ (i.e., assuming no change) to handle dichotomous incomplete data. Continuous outcome data will be analysed with Multi-level analyses. Multi-level analyses with full information maximum likelihood (FIML) estimation use all available data and allow intention-to-treat analyses including all participants with incomplete data and participants who dropped out during the study. Continuous variables will be transformed into *Z*-scores. In this way, the parameter estimates can be interpreted as a measure of effect: i.e., as Cohen’s *d* for dichotomous predictors and as *r* for continuous predictors. Outliers will be identified. Analyses will be run twice: once in which all original scores will be included and once in which outliers will be changed to *Z*-scores (-) 3.29. Dependent variables will be level of FoC, labour pain and willingness to accept obstetrical interventions without medical indications. Predictors will be the different time measurements (T2, T3, and T4 against T1) and condition (MBCP versus FoCC). Interaction effects of time X condition will be added to the model to examine which programme is more effective over time.

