### Inclusion criteria

Participants are primiparous and multiparous women, aged ≥18, fluent in the Dutch or English language who are more than 16 weeks and less than 26 weeks pregnant at baseline, and are experiencing a high level of FoC (W-DEQ-A ≥66) [9]. If an eligible woman agrees to participate, her partner will be asked to take part in the study as well. As ‘partner’ we refer to the father or co-parent of the expected baby, or a significant other person related to the pregnant woman who will be present at the birth. Pregnant women may enter the study without a partner or a significant other.

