### Outcome measures

In this study several assessment tools will be used. Some measures were translated specifically for this study. Translations were made in accordance with the scientific standards for translating questionnaires [60] and permission to translate has been given by the original authors. Table 4 presents an overview of the primary and secondary outcome measures and the time points of study assessments.

**Table 4 Tab4:** Overview of Measures, Outcomes, and Corresponding Measurement Occasions for the (pregnant) Women and their Partners

Measure	Outcome domain	Measurement occasion			
		T1	T2	T3	T4
W-DEQ-A	Anticipated fear of childbirth	X	X		
W-DEQ-B	Experienced fear of childbirth			X	X
PDSS^a^	Perinatal disaster scenarios	X	X	X	X
PAFS	Responses to anxiety and fear	X	X	X	X
CLP	Catastrophizing of labour pain	X	X		
LPAQ	Acceptance of labour pain	X	X		
VAS	Labour pain intensity	X	X	X	
WAOI^a^	Willingness to accept interventions	X	X		
DASS-21^a^	Depression, anxiety and stress	X	X	X	X
PSS^a^	Stress	X	X	X	X
EPDS	Prenatal/postnatal depression	X	X	X	X
PES-US	Uplifting experience of pregnancy	X	X		
NPSI-SF^a^	Parenting stress			X	X
EQ-5D^a^	Quality of life	X	X	X	X
PSQI^a^	Sleep quality	X	X	X	X
HSDQ-I^a^	Insomnia	X	X	X	X
ISVIS^a^	Interpretation of infant sleep	X	X	X	X
BISQ	Infant sleep			X	X
MAF^a^	Fatigue	X	X	X	X
SIL^a^	Satisfaction with birth			X	X
MR	Medical report about perinatal period				X
BSES-SF	Breastfeeding self-efficacy			X	X
FFMQ^a^	Mindful awareness	X	X	X	X
IM-P^a^	Mindful parenting skills			X	X
SCS-SF^a^	Self-compassion	X	X	X	X
PHCQ	Costs in and outside the healthcare sector	X	X	X	X

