Sleep quality will be assessed by the Pittsburgh Sleep Quality Index (PSQI) [74] with additional sleep efficiency questions, and the Insomnia scale derived from the Holland Sleep Disorders Questionnaire (HSDQ-I) [75]. Sleep quality of the infant will be measured by the Dutch version of the Infant Sleep Vignettes Interpretation Scale (ISVIS) [76], ([name], [name], [name], [name]: Dutch version of ISVIS, unpublished) [76], and by the Brief Infant Sleep Questionnaire (BISQ) [77]. Furthermore, fatigue will be assessed by the Multidimensional Assessment of Fatigue (MAF) [78]. Satisfaction with childbirth will be assessed by the Dutch version of the Salomon’s Item List (SIL) [79]﻿, (﻿﻿﻿[name], [name], [name], [name]: Dutch version of SIL, unpublished﻿﻿). Birth outcome for mother (e.g., modus partus) and infant (e.g., birth weight and APGAR score) will be derived from the medical report (MR). And last, breastfeeding self-efficacy of the mother will be assessed by the Dutch version of the Breastfeeding Self-Efficacy Scale-Short Form (BSES-SF) [80]﻿, ([name], [name], [name], [name]: Dutch version of BSES-SF, unpublished﻿).

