Some limitations to this study design need to be considered. First, the quasi-experimental study design creates less homogeneous groups then with full randomization (RCT) and permits a greater risk of bias due to potential alternation and allocation problems. To work with this, we adopted the recommendations for designing the Q-RCT studies from the Cochrane Handbook for Systematic Reviews of Interventions [86]. Due to the steadily increasing gestational age, dependency on recruitment speed and efficiency, and the required size of approximately six participants in the intervention group, we are obliged to use the quasi-randomization procedure in order to be able to conduct this study efficiently. A second limitation is the uncertainty of the power of this study due to the unknown effect size of the comparison group. To cover this limitation, we have chosen to downsize the expected large effect size of MBCP as shown in Duncan and [name]’s [40] study to a medium effect size in order to not under-power our study. An additional limitation is the potentially sizable dropout of participants due to their possibly strong preferences for one of the study’s interventions, the nine weeks duration of the programmes, and the relatively long and direct follow up after the birth. As a retention strategy we provide the participants with a financial incentive (€50) for completing the measurements following the birth.

Among the strengths of this study are the clinical-based experimental design, the extensive cognitive-emotional and behavioural measurements in pregnant women and their partners during the entire perinatal period, and the representativeness of the study sample as well as the generalizability of the study’s results. The complex and innovative measurements of FoC in this study are an important strength in research on FoC not only in pregnant women but also in their partners.

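### Carrying the last observation forward is the only stated rule for incomplete dichotomous data: it cannot be applied to birth outcomes, and for repeated dichotomous outcomes it creates an arm difference if dropout is unequal

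*Protocol article*

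**What the plan says.** All references are to the protocol article.

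- **Dichotomous outcomes (Primary analyses).** "Dichotomous outcome data will be analysed using Chi-square tests or logistic regression", with last observation carried forward, explained as "i.e., assuming no change) to handle dichotomous incomplete data". The section names no other method and no sensitivity analysis for missing data. Its only repeat analysis concerns outliers.
- **Continuous outcomes (same section).** Multilevel models with full information maximum likelihood (FIML), whose "estimation use all available data and allow intention-to-treat analyses including all participants with incomplete data".
- **Birth outcomes (Secondary outcome measures).** "Birth outcome for mother (e.g., modus partus) and infant (e.g., birth weight and APGAR score) will be derived from the medical report (MR"). In Table 4 the row "Medical report about perinatal period" is marked at T4 only.
- **Fear of childbirth (Table 4).** W-DEQ-A is scheduled at T1 and T2, and W-DEQ-B at T3 and T4.
- **Entry (Inclusion criteria).** Women "are experiencing a high level of FoC (W-DEQ-A ≥66").
- **Dropout (Discussion).** "An additional limitation is the potentially sizable dropout of participants due to their possibly strong preferences" and to the length of the programmes and of follow-up. No rate is given for either arm.

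**The concern.** The rule has two separate problems.

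First, LOCF needs an earlier value of the same measure. Mode of birth is observed once, so the rule gives no instruction for a woman whose medical report is missing. No change also has no meaning for a birth.

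Second, where a dichotomous outcome is repeated, a woman lost between T1 and T2 is scored as if the programme had done nothing, and the chi-square test then counts that guess as data. If a fear cut-off were analysed after birth, carrying T2 into T3 or T4 would also put a W-DEQ-A value (anticipated fear) in place of a W-DEQ-B value (experienced fear).

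The two programmes ask for very different commitment: nine weekly classes plus home practice of 30 minutes a day on six days a week, against two one-hour consultations. Unequal dropout is therefore plausible. If it occurs, LOCF converts a difference in retention into an apparent difference in effect. A dichotomised score would also rest on a different missing-data assumption from the continuous score for the same missing women.

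**Working it through.** **Step 1: the plan's own figure.** The LOCF sentence carries no number. The relevant stated figure is 64 women per arm, for 80% power, 5% alpha and correlation 0.5. Taking the medium effect as d = 0.5 and the test as two-sided (both assumptions), a change score has SD √(2(1 − 0.5)) = 1. The two-sample t calculation then gives 63.8, so 64 per arm, with power 0.801. The figure reproduces and is used below. The 30% in the Sample size section is a referral rate and is not used here as a dropout rate.

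**Step 2: can the rule be applied?**

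| Dichotomous outcome | Occasions in Table 4 | Earlier value to carry? |
|---|---|---|
| Mode of birth (medical report) | T4 | None |
| Fear cut-off at T2, if used (W-DEQ-A) | T1, T2 | T1 |
| Fear cut-off at T3, if used (W-DEQ-B) | T3, T4 | None of the same version; only W-DEQ-A |
| Fear cut-off at T4, if used (W-DEQ-B) | T3, T4 | T3; otherwise only W-DEQ-A |

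**Step 3: size of the artefact with no true difference.** Let p be the true response rate in both arms, d an arm's dropout (unrelated to outcome), and q the share already below the cut-off at T1. With T1 as every dropout's last value:

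LOCF rate = p(1 − d) + qd, so the artefact = (p − q) × (difference in dropout).

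False-positive rates come from exact enumeration of the uncorrected chi-square test at 64 per arm. All dropout and response rates are assumptions. With p = 50% and q = 0:

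| Dropout, arm 1 v arm 2 | LOCF rates | Artefact | False-positive rate |
|---|---|---|---|
| 20% v 20% | 40% v 40% | 0 | 0.054 |
| 20% v 10% | 40% v 45% | 5 points | 0.091 |
| 30% v 15% | 35% v 42.5% | 7.5 points | 0.148 |
| 30% v 10% | 0.50 × 0.70 = 35% v 0.50 × 0.90 = 45% | 10 points | 0.220 |
| 40% v 10% | 30% v 45% | 15 points | 0.432 |

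At 30% v 10%, p = 30% gives 21% v 27% (6 points, 0.125) and p = 70% gives 49% v 63% (14 points, 0.358).

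**Step 4: what shrinks it (p = 50%, dropout 30% v 10%).**

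- Half the dropouts leave after T2 and carry a T2 value with the same response rate. The effective loss is 15% v 5%, the rates are 42.5% v 47.5%, and the false-positive rate is 0.086.
- q = 20%. Arm 1 is 0.35 + 0.20 × 0.30 = 41% and arm 2 is 0.45 + 0.20 × 0.10 = 47%. The artefact is 6 points and the false-positive rate 0.105.

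**Step 5: comparison with using the observed data.** Under the same assumptions, an observed-case test (45 v 58 women at 30% v 10% dropout) has a false-positive rate of 0.050 for p = 30%, 50% and 70%.

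**Step 6: equal dropout with a real effect.** A true 50% v 25% with 30% dropout in both arms becomes 35% v 17.5%, and power falls from about 0.85 to 0.63.

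**The case against.** **The illustrated outcome is not declared.** No section defines falling below 66 as an outcome. The named dependent variables are level of fear, labour pain and willingness to accept interventions, measured mainly by scale scores that go to FIML. The nearest responder measure, in the Cost-effectiveness section, is not tied to the cut-off and is not said to use LOCF. This stands. A reader might infer that the main fear analysis is compromised; the documents do not support that.

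**Early dropouts are not necessarily scored as high fear.** Screening sets eligibility, and the Design section places the T1 questionnaires after inclusion. If T1 is a separate administration, some women may already score below 66. This stands and is why q appears in the working.

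**Unequal dropout is not predicted.** The Discussion calls dropout only potentially sizable, cites the duration of both programmes, and describes a retention payment. A reader might infer that the protocol expects more loss from the mindfulness arm; it does not say so. That is an inference from burden. If it is right, a recovery artefact would count against the mindfulness programme rather than manufacture the hypothesised benefit.

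**Birth outcomes may be rarely missing.** They are secondary and come from medical reports. A reader might infer that LOCF biases mode of birth. It cannot, since there is nothing to carry; the rule is unworkable there, not biased.

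**Different methods for different outcome types are not a contradiction.** Agreed: the protocol claims no common assumption. This is inconsistent practice, not an error of logic.

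What the objections leave standing is that LOCF is the fixed and only stated method for these data. It is therefore not a detail left to an analysis plan.

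**Conclusion.** The point holds in a limited form. For single-occasion birth outcomes, the stated rule cannot be carried out. That follows from Table 4 alone and needs no assumption about dropout.

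For any repeated or dichotomised outcome, the rule biases the arm comparison whenever dropout differs by arm and the carried value differs from the expected later one. At 30% v 10% dropout, with T1 always the last value and no woman below the cut-off at T1, the artefact is 6 to 14 points and the false-positive rate 0.125 to 0.358 for true response between 30% and 70%. The central case is 10 points and 0.22. Relaxing either the last-value or the T1 assumption as in Step 4 brings the central case down to about 0.09 to 0.11. With equal dropout and no true effect there is no artefact, although a real effect would be diluted.

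The direction and size in this trial are unknown, because the protocol gives no dropout by arm and does not list its dichotomous outcomes. The continuous primary scale scores are untouched. The change should be made, but it does not threaten the main fear analysis.

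**What to change.** In Primary analyses, replace LOCF as the main method:

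- **Repeated dichotomous outcomes:** a mixed-effects logistic model using all available data, or multiple imputation using arm and baseline values followed by logistic regression.
- **Once-only birth outcomes:** logistic regression, with multiple imputation where the medical report is missing.
- **No change:** keep only as a sensitivity analysis, and only where an earlier value of the same measure exists. W-DEQ-A should not stand in for W-DEQ-B.

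The cost is revised wording and a little more analysis work, with no new data. The replacement assumes data are missing at random, which preference-driven dropout may violate. FIML already makes the same assumption for the continuous outcomes, so the change also brings the two outcome types into line.

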### Aims

The ‘I’ve Changed My Mind study’ is designed with four primary aims: 1) to assess the effects of MBCP, as compared to FoCC, on the primary outcome measures of a) FoC, b) labour pain, and c) willingness to accept obstetrical interventions without medical indications in pregnant women with a high level of FoC; 2) to assess the effects of MBCP, as compared to FoCC, on the secondary outcome measures of a) anxiety, b) depression, c) general stress, d) pre- and postnatal stress, e) quality of life, f) sleep quality of women, her partner and infant, g) pre- and postnatal fatigue, h) satisfaction with childbirth, i) birth outcome for mother and child, and j) breastfeeding self-efficacy in pregnant women with a high level of FoC and their partners; 3) to examine overall mindful awareness, self-compassion, and catastrophic beliefs as possible mediating mechanisms underlying the effectiveness of MBCP; 4) to assess the costs of health care use due to FoC and cost-effectiveness of MBCP as compared to FoCC. These four aims will be examined in three time periods: a) during pregnancy, b) after labour, and c) during the maternity leave period following the birth.

It is hypothesized that participants in the MBCP group, as compared to those in the FoCC group will a) show larger and longer lasting effects on all primary and secondary outcome measures, b) demonstrate increased overall mindful awareness and self-compassion, and decreased catastrophic beliefs, and c) have lower FoC related health care costs, indicating that MBCP is more cost-effective than FoCC.

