### Primary outcome measures

Primary outcome measures are (a) FoC, (b) labour pain, and (c) willingness to accept obstetrical interventions without medical indications.

The complexity of FoC will be measured by three instruments, namely the W-DEQ- A and B [3], the newly developed Perinatal Disaster Scenarios Scale (PDSS), ([name], [name], [name], [name]: PDSS, unpublished), and the experimental Perinatal Anxiety/Fear Scale (PAFS), ([name], [name], [name]: PAFS, unpublished). First, anticipated and experienced levels of FoC will be assessed with the 33 items self-report W-DEQ- A and B covering several domains of FoC: (a) general fear, (b) negative appraisal, (c) loneliness, (d) lack of self-efficacy, (e) lack of positive anticipation, and (f) concerns about the child [61]. Second, the individual perinatal fear-eliciting beliefs, in pregnant women and their partners, will be assessed by the PDSS. We developed the PDSS, which is based on the Social Phobia Belief Scale (SPBS) [62], for this study in order to describe catastrophic beliefs about childbirth and future-related events that are eliciting fear (maximum of 3 beliefs). The PDSS assesses the probability of actual occurrence of those catastrophic events, the severity, and the ability to cope with them in the future on the Visual Analogue Scale (VAS) [63], (0–100 %). And third, to assess responses to anxiety and fear in pregnant women we will administer the experimental PAFS based on the Dimensional Anxiety Self-report of Social Phobia level 3 DSM-IV [64].

Subsequently, three instruments will be included to assess labour pain. First, anticipated and experienced cognitive and emotional components of labour pain will be assessed by the 13 item self-report Catastrophizing Labour Pain (CLP) subscale derived from the Labour Pain Cognitions and Coping List (LPCCL) [65], the 20 item self-report Labour Pain Acceptance Questionnaire (LPAQ), ([name], [name], [name], [name], [name]: LPAQ, unpublished), an adaptation of the Chronic Pain Acceptance Questionnaire (CPAQ) [66], and the expected and experienced severity of labour pain will be assessed by the VAS [63] (0–10).

Last, the willingness to accept obstetrical interventions without medical indications will be assessed by the Dutch version of the Willingness to Accept Obstetrical Interventions measure (WAIO) [67], ([name], [name], [name], [name]: Dutch version of WAIO, unpublished).

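### One primary model (T2, T3 and T4 against T1) is stated for all primary outcomes, but the measurement schedule supports it unchanged for only two of seven primary instruments

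*Protocol article*

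**What the plan says.** The protocol article, under Statistical analyses (Primary analyses), names all three primary domains as outcomes of one model: "Dependent variables will be level of FoC, labour pain and willingness to accept obstetrical interventions without medical indications". The time and condition terms follow: "Predictors will be the different time measurements (T2, T3, and T4 against T1) and condition (MBCP versus FoCC". The test of interest is the interaction: "Interaction effects of time X condition will be added to the model to examine which programme is more effective over time". No exception is made for any instrument. Continuous variables are to be converted to Z-scores so that coefficients can be read as effect sizes.

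Table 4 (Outcome measures) sets the schedule. T1 and T2 fall before birth, T3 and T4 after it. W-DEQ-A, labelled "Anticipated fear of childbirth", is given at T1 and T2. W-DEQ-B, labelled "Experienced fear of childbirth", is given at T3 and T4. WAOI, labelled "Willingness to accept interventions", and the pain scales CLP and LPAQ are given at T1 and T2 only. The pain VAS is given at T1, T2 and T3. PDSS and PAFS are given at all four waves.

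Primary outcome measures says that "anticipated and experienced cognitive and emotional components of labour pain will be assessed by the 13 item self-report Catastrophizing Labour Pain (CLP) subscale", and names the LPAQ in the same list. It describes the VAS as covering expected and experienced pain severity. Aims states: "These four aims will be examined in three time periods", and hypothesises larger and longer lasting effects of MBCP on every primary outcome.

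**The concern.** The stated model needs four waves of one variable. Most primary instruments do not have them. WAOI is the only instrument for the third primary outcome and stops before birth, so nothing can be said about lasting effects on that outcome.

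For W-DEQ, a T3-against-T1 or T4-against-T1 term compares what a woman went through with what she had expected, on two versions of a questionnaire. The T3-against-T1 term for the VAS has the same feature. Such a time effect mixes the switch from expectancy to experience with any change in fear or pain.

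If the sections are not reconciled, the analyst must decide after the fact which waves count, whether versions A and B are pooled, and how they are standardised.

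**Working it through.** **Step 1. Which terms can be estimated.** The stated model has 8 fixed effects: an intercept, 3 time terms, condition and 3 interactions. Each instrument's Table 4 waves determine how many can be estimated (the rank of the design matrix).

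| Instrument | Waves | Estimable of 8 |
|---|---|---|
| PDSS | T1–T4 | 8 |
| PAFS | T1–T4 | 8 |
| W-DEQ, A and B joined | A at T1/T2, B at T3/T4 | 8 |
| W-DEQ-A alone | T1, T2 | 4 |
| Pain VAS | T1–T3 | 6 |
| CLP | T1, T2 | 4 |
| LPAQ | T1, T2 | 4 |
| WAOI | T1, T2 | 4 |

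Counting W-DEQ as one, there are 7 primary instruments. Four (CLP, LPAQ, VAS, WAOI) lack a required wave. W-DEQ is a fifth that does not fit without joining two versions. Two fit unchanged. Full information maximum likelihood does not help, because nobody is measured at an unscheduled wave.

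**Step 2. What the joined W-DEQ contrast estimates.** Write A1 for the mean of version A at T1 and B3 for the mean of version B at T3.

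- Time effect in the FoCC arm: B3(FoCC) − A1(FoCC). This contains the version switch.
- Interaction: [B3(MBCP) − A1(MBCP)] − [B3(FoCC) − A1(FoCC)] = [B3(MBCP) − B3(FoCC)] − [A1(MBCP) − A1(FoCC)].

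If the arms are comparable at T1, the last bracket has expectation zero and the interaction equals the between-arm difference on version B. A simulation confirms this (64 per arm, correlation 0.3, true arm effect −0.50, common shift −0.80, 4,000 runs). The mean interaction estimate was −0.50 and the mean time effect −0.80, so the common shift goes entirely into the time effect.

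**Step 3. The plan's own sample size.** Inputs from Sample size: 64 per arm, 80% power, 5% alpha, correlation 0.5, interaction test. Assumed because not stated: d = 0.5 for a medium effect, and a two-sided test. The SD of a two-wave change is s = √(2(1 − r)); at r = 0.5, s = √(2 × 0.5) = 1. The noncentrality is (d/s)√(n/2) = 0.5 × √32 = 2.83 on 126 degrees of freedom, giving power 0.801. The planned 128 is reproduced for a two-wave change contrast.

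**Step 4. Precision when T1 is expectancy and T3 is experience.** The document gives no correlation for this pairing, so a range is shown. For adjustment on T1, s = √(1 − r²).

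| r (assumed) | s, change | Power, change from T1 | Power, adjusted for T1 |
|---|---|---|---|
| 0.2 | √1.6 = 1.265 | 0.60 | 0.82 |
| 0.3 | √1.4 = 1.183 | 0.66 | 0.84 |
| 0.4 | √1.2 = 1.095 | 0.73 | 0.87 |
| 0.5 | √1.0 = 1.000 | 0.80 | 0.90 |
| 0.6 | √0.8 = 0.894 | 0.88 | 0.94 |

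Example at r = 0.3: change, 0.5/1.183 = 0.423, × √32 = 2.39, power 0.66; adjusted, s = √0.91 = 0.954, 0.5/0.954 = 0.524, × √32 = 2.97, power 0.84.

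**Step 5. The text against the table.** Primary outcome measures assigns experienced labour-pain components to CLP and LPAQ, yet Table 4 schedules neither after birth. The hypothesis of longer lasting effects on all primary outcomes cannot be examined for WAOI, CLP or LPAQ on this schedule, and cannot be examined at T4 for the VAS.

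**The case against.** The strongest reply is that an article compresses its analysis into a paragraph, and that terms for unmeasured waves simply drop out. That is partly right. A reader might infer that the primary analysis cannot be run at all, and the documents do not support this: T2 against T1 compares like with like for every instrument given at those waves, and the reduced model is easy to fit. Still, the article positively states one model without exception, and its own table contradicts it. This is more than detail left to a fuller plan.

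Second, nothing says outright that versions A and B are to be joined; the outcome is called only the level of fear. Joining is implied by the T3 and T4 terms, not declared. That stands, and it is why the treatment of W-DEQ needs stating.

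Third, a reader might infer that the post-birth treatment effect on W-DEQ is biased or uninterpretable. Step 2 shows otherwise when the arms are comparable at T1. The reservation is that allocation is by alternation, and the Discussion itself concedes a greater risk of bias.

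Fourth, the power loss depends on a correlation nobody has supplied. At the plan's 0.5 there is no shortfall, and above 0.5 power exceeds 80%. A claim that the trial is underpowered on this ground would be unsupported.

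Finally, the sentence about three time periods concerns aims, not each instrument, and aim 1 does have post-birth data from W-DEQ-B, PDSS, PAFS and the VAS. The overreach lies in the hypothesis covering all primary outcomes.

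**Conclusion.** The point holds as a should-fix. The stated model and the schedule disagree for five of seven primary instruments: four lack waves, and W-DEQ changes version at birth. The post-birth time effects on W-DEQ (T3, T4) and the VAS (T3) cannot be read as change in fear or pain, and a Z-score spanning versions A and B has no defined meaning. No bias in the between-arm contrast has been shown, provided the arms are comparable at T1.

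The effect on precision is conditional. With d = 0.5, 64 per arm and a two-sided 5% test, change from T1 gives 0.60 to 0.88 over correlations of 0.2 to 0.6, while adjustment for T1 gives 0.82 to 0.94. At the plan's own 0.5 the gain is from 0.80 to 0.90. The documents do not show whether Table 4 or the text is right about CLP and LPAQ after birth.

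**What to change.** State the contrasts per instrument in Primary analyses:

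1. W-DEQ-A, WAOI, CLP, LPAQ and expected pain: compare arms at T2, adjusted for the T1 score.
2. W-DEQ-B: a separate outcome at T3 and T4, with condition, time and their interaction, adjusted for T1 W-DEQ-A.
3. Experienced pain on the VAS: a separate T3 outcome, adjusted for T1 expected pain.
4. PDSS and PAFS: a T2 to T4 model, adjusted for T1.

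Standardise each W-DEQ version separately. Keep the change-from-T1 analysis as a sensitivity check, because quasi-random allocation does not assure baseline balance.

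Reconcile Primary outcome measures with Table 4 on experienced CLP and LPAQ, and limit the hypothesis of longer lasting effects in Aims to outcomes measured after birth.

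Items 1 to 4 cost only wording, since every variable they use is already scheduled. The exception is CLP and LPAQ: if the text rather than the table is right, post-birth administrations would have to be added.
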